### Study design

This study is an open-label phase II multi-centre randomized trial, and is designed to assess two potential treatment de-escalation approaches, comparing each to a historical control, with the potential goal of evaluating one or both compared to standard CRT in a subsequent phase III trial. The required sample size is 140 patients. Participating centres will be tertiary, academic hospitals or radiotherapy treatment centres in Canada (updated list of participating centres available on clinicaltrials.gov: identifier NCT03210103). Patients will be randomized between a primary RT-based approach (Arm 1) vs. a primary surgical approach (Arm 2) in a 1:1 ratio using a permutated block design (Fig. 1). There will be one stratification factor: smoking status (< 10 vs. ≥ 10 pack-years). Arm 1 of this trial is based on the chemoradiation arm of HN002 (60 Gy ± concomitant weekly cisplatin based on clinical nodal disease) [15], and Arm 2 is similar to the treatment paradigm of ECOG-3311 (TOS ± adjuvant RT (50–60 Gy) based on risk factors) [16].

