#### Sample size calculation

The 2-year OS in each arm, based on the results of ORATOR, is estimated to be 94%. A 2-year OS of < 85% will be considered inadequate. In order to differentiate an OS of 94% vs. 84% using a 1-sided one-sample binomial test, with 80% power and alpha of 0.05, with 10% dropout, 70 patients are needed in each arm (140 total).

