### Data safety monitoring committee

The data safety monitoring committee (DSMC), consisting of at least one surgical oncologist, one radiation oncologist, and one medical oncologist not involved in the study and without competing interests, will meet bi-annually after study initiation to review toxicity outcomes. The DSMC can recommend modification of the trial based on toxicity outcomes.

After half of the patients are enrolled and followed for 6 months, one interim analysis will take place. For this interim analysis, OS at 2-years will be calculated for each arm. The DSMC may recommend cessation or modification of the trial if any of these two criteria are met:
The rate of grade 5 toxicity definitely related to treatment is > 5% in either armThe upper bound of the 95% confidence interval of OS at 2 years does not include 94%.

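### The interim OS criterion needs a 2-year estimate at a look triggered by 6 months of follow-up, so it may not be computable or may rest on few patients

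*Protocol article*

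**What the plan says.** All of the following is in the protocol article.

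- **Timing** (Data safety monitoring committee): "After half of the patients are enrolled and followed for 6 months, one interim analysis will take place". Half of 140 is 70 patients, about 35 per arm under 1:1 allocation.
- **Quantity** (same section): "For this interim analysis, OS at 2-years will be calculated for each arm".
- **Consequence** (same section): "The DSMC may recommend cessation or modification of the trial if any of these two criteria are met". One criterion is a grade 5 toxicity rate above 5% in either arm, counting events definitely related to treatment. The other is that the upper 95% confidence bound of 2-year OS falls short of 94%.
- **Design values** (Sample size calculation): 94% is the expected 2-year OS in each arm. The text adds "A 2-year OS of < 85% will be considered inadequate", and the sizing statement reads "In order to differentiate an OS of 94% vs. 84% using a 1-sided one-sample binomial test".

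The article gives no accrual rate or accrual period. It does not say how a 2-year figure is to be obtained at this look.

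**The concern.** The trigger and the quantity do not match. A look defined by 6 months of follow-up guarantees only 6 months per patient. A 24-month survival proportion with a confidence interval needs patients observed to 24 months, unless a model carries the curve forward, and no model is named.

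The stakes lie in what the other safeguards leave out. The twice-yearly committee meetings are described as reviews of toxicity, and the toxicity criterion counts only grade 5 events definitely related to treatment. Deaths from cancer that recurs after reduced treatment are a central risk in a de-escalation trial, and OS is the primary endpoint. Of the two listed criteria, only the OS one covers such deaths.

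**Working it through.** **1. The plan's own figure.** Exact one-sample binomial test, null 84%, alternative 94%, one-sided alpha 0.05. The smallest n with at least 80% power is 63: success needs 58 or more survivors (alpha 0.0493, power 0.824). Allowing for 10% dropout, 63/0.9 = 70 per arm, which matches. The final test therefore tolerates at most 5 deaths (58/63, or 65/70).

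**2. Longest follow-up at the interim.** Let total accrual take A years at a uniform rate (an assumption). The 70th patient enters at A/2, and the look comes 0.5 years later.

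Longest follow-up = A/2 + 0.5 years. This exceeds 2 years only if A > 3.

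**3. Patients who can contribute at 24 months.** In months, follow-up is spread evenly from 6 to 6 + 6A, so the number per arm with at least 24 months of potential follow-up is 35 × (6A − 18)/(6A).

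| Total accrual | Follow-up range | Potential 24-month follow-up, per arm |
|---|---|---|
| 2 years | 6-18 months | 0 |
| 3 years | 6-24 months | 0 |
| 4 years | 6-30 months | 35 × 6/24 = 8.75 |

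At 4 years, the number still alive and at risk at 24 months is 8.75 × 0.94 = 8.2 or 8.75 × 0.85 = 7.4. At 2 or 3 years, the Kaplan-Meier value at 24 months was undefined in over 99% of simulated interims.

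**4. Expected deaths per arm** (constant hazard, so survival to t months is S^(t/24), where S is the 2-year OS).

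- Every patient at exactly 6 months: 35 × (1 − 0.94^0.25) = 0.5; 35 × (1 − 0.85^0.25) = 1.4.
- 4-year accrual, averaging over 6 to 30 months: 1.6 at true OS 94%, 4.0 at 85%. As a check at the mean of 18 months: 35 × (1 − 0.94^0.75) = 1.6; 35 × (1 − 0.85^0.75) = 4.0.

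**5. The 94% limit when data are mature.** With 35 patients per arm and complete 2-year data, the Clopper-Pearson upper limit is 95.2% for 30/35 and 93.4% for 29/35. The criterion is met at 6 deaths, with observed OS of 82.9%. Step 1 allows at most 5 deaths in the whole arm, so an arm that meets the criterion has already lost its final test. With a Wilson interval it is met at 5 deaths (observed 85.7%), when no further death is affordable.

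**6. Observable alternatives, keeping 94%.**

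- *12-month OS:* √0.94 = 0.970 under constant hazard. With 2-, 3- or 4-year accrual, 35 × (6A − 6)/(6A) = 17.5, 23.3 or 26.3 patients per arm have 12 months of potential follow-up.
- *Person-time:* 94% at 2 years is a rate of −ln(0.94)/2 = 0.0309 deaths per year. With 4-year accrual and about 50 person-years per arm, 5 deaths have an exact Poisson lower limit of 1.62. Then 1.62/50 = 0.0324 per year, and the upper OS bound is exp(−2 × 0.0324) = 93.7%, so the criterion is met. Simulation (40,000 runs, 35 per arm) gave these chances of meeting it:

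| Total accrual | True OS 94% | True OS 85% |
|---|---|---|
| 2 years | 2% | 28% |
| 3 years | 1% | 25% |
| 4 years | 2% | 35% |

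**The case against.** **Accrual may be slow.** The accrual period is an assumption here. With 4-year accrual a Kaplan-Meier estimate exists at 24 months. In simulation with a log-log interval, the written criterion was met 3% of the time at true OS 94% and 41% at 85%, close to the mature-data figures of 2% and 43% (Clopper-Pearson). This stands: the rule fails outright only if total accrual is about 3 years or less. But the article does not fix the look so as to exclude that case.

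**The estimator can be left to another document.** A full protocol, analysis plan or committee charter may name one, and a parametric estimate is computable at this look. That is fair, so the point is not that an estimator is missing. It is that the stated trigger and the stated quantity do not fit together unless a modelling assumption is added.

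**The rule is non-binding, and other monitoring exists.** Both are true. Toxicity review and rapid reporting of severe treatment-related events continue regardless. They do not cover deaths from recurrent cancer.

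**A stronger reading.** A reader might infer that 94% is the wrong comparator, because the trial calls an arm inadequate only below 85%. With mature data an arm with true OS of 90% would meet the criterion 13% of the time (27% with Wilson). The documents do not support calling this an error. The rule asks whether the data exclude the design alternative, which is a coherent futility question, and it agrees with the final test (step 5). Moving the same 95% bound to 85% would require 11 deaths of 35 and would be met only 1.1% of the time at true OS 85%. A looser one-sided 80% bound against 85% would need 8 deaths and would alert about 19% of the time at true OS 84%, against about 50% for the written rule.

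**Conclusion.** The timing point holds. Under uniform accrual, no patient has more than 24 months of follow-up at the interim unless total accrual exceeds about 3 years. At 4 years, about 7-8 of 35 per arm are still at risk at 24 months, with about 1.6 expected deaths per arm at true OS 94% and 4.0 at 85%. A non-parametric 2-year OS is then either not estimable or rests on few patients, so the one listed criterion covering deaths not definitely related to treatment may not work as written.

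This rests on assumed uniform accrual, about 35 patients per arm and, for the death counts, a constant hazard. The mismatch between trigger and quantity is on the face of the text and needs none of these. The 94% limit itself is sound.

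**What to change.** Keep the look where it is and state the criterion in terms of what can be observed then, in one of two ways:

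- deaths and person-time per arm, converted to 2-year OS under a stated constant-hazard assumption, with the upper 95% bound still compared with 94%; or
- 12-month OS per arm, with its upper 95% bound compared with 97.0%.

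Alternatively, keep 2-year OS and tie the look to a stated amount of 24-month follow-up.

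Whichever is chosen, name the estimator and interval method and report how often the criterion would be met at a few true OS values. Calling the OS criterion a futility limit would help the committee interpret a crossing.

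The cost is wording in the protocol or committee charter, with no new data. The first two options rely on the constant-hazard assumption and the third gives a later look. Sensitivity stays modest: the person-time version is met about 25-35% of the time at true OS 85%, because few deaths will have occurred.

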#### Biomarker studies

All of the biomarker studies described in this section will be performed in [name] laboratory located at the London Regional Cancer Program, in London, Ontario. All specimens will be labeled solely with the patient’s unique study identifier number, stored in a secure facility at London Health Sciences Centre (LHSC), and will be accessed only by clinical trial staff. Details are provided in Additional file 4. Ten mL of blood shall be drawn pre-operatively into a heparinized (green top) tube and directly transported to [name] lab. At the end of the study pre-treatment formalin fixed paraffin embedded (FFPE) primary site biopsy specimens will be retrieved in 10 slides 8 μm thick as well as three 1 mm core punch biopsies from the FFPE blocks and transported to [name] lab. For patients treated at the lead centre (LRCP) and randomized to primary surgery a fresh frozen specimen will be collected. Specifically, at the time of operation the main specimen will be taken to pathology frozen section room and a portion from the center of the specimen will be taken with the assistance of the pathologist and frozen at − 80 degrees Celsius. This will be transported to [name] lab.

##### Human papillomavirus testing

P16 testing (which is an excellent surrogate marker of HPV status) is required for enrollment. This will be done through the routine pathology laboratories as per current routine clinical care. The accompanying biomarker study will determine HPV status by real-time PCR, not for the purposes of randomization, but to confirm the accuracy of p16 results and also for subtyping of HPV strain. Pre-treatment FFPE primary site biopsy specimens will be retrieved in 10 slides 8 μm thick from the FFPE blocks. DNA will be extracted from the specimens for HPV testing by real-time PCR.

##### Whole genome sequencing analysis

DNA will be extracted either from fresh tumor or from formalin fixed specimens for patients undergoing TOS, as well as 10 mL of venous blood drawn prior to the initiation of treatment. Specimens yielding DNA of adequate quantity and quality (> 5 μg, OD between 1.8 and 2.0) will be subjected to high-throughput sequencing and gene copy number.

## Ethical considerations

The Principal Investigator will obtain ethical approval and clinical trial authorization by competent authorities according to local laws and regulations.

### Institutional Review Board (IRB) / Research Ethics Board (REB)

The protocol (and any amendments), the informed consent form, and any other written information to be given to subjects will be reviewed and approved by a properly constituted Institutional Review Board (IRB)/Research Ethics Board (REB), operating in accordance with the current federal regulations (e.g., Canadian Food and Drug Regulations (C.05.001); US Code of Federal Regulations (21CFR part 56)), ICH GCP and local regulatory requirements. A letter to the investigator documenting the date of the approval of the protocol and informed consent form will be obtained from the IRB/REB prior to initiating the study. Any institution opening this study will obtain REB IRB/REB approval prior to local initiation.

### Informed consent

The written informed consent form is to be provided to potential study subjects (Additional file 5) should be approved by the IRB/REB and adhere to ICH GCP and the ethical principles that have their origin in the Declaration of Helsinki. The investigator is responsible for obtaining written informed consent from each subject, or if the subject is unable to provide informed consent, the subject’s legally acceptable representative, prior to beginning any study procedures and treatment(s). The investigator should inform the subject, or the subject’s legally acceptable representative, of all aspects of the study, including the potential risks and benefits involved. The subject will be given ample time and opportunity to ask questions prior to deciding about participating in the study and be informed that participation in the study is voluntary and that they are completely free to refuse to enter the study or to withdraw from it at any time, for any reason.

The informed consent will be signed and dated by the subject, or the subject’s legally acceptable representative, and by the person who conducted the informed consent discussion. A copy of the signed and dated written informed consent form will be given to the subject or the subject’s legally acceptable representative. The process of obtaining informed consent will be documented in the patient source documents.

### Confidentiality

The names and personal information of study participants will be held in strict confidence. All study records (CRFs, safety reports, correspondence, etc.) will only identify the subject by initials and the assigned study identification number. The data coordinator will maintain a confidential subject identification list (Master List) during the course of the study. Access to confidential information (i.e., source documents and patient records) is only permitted for direct subject management and for those involved in monitoring the conduct of the study (i.e., Sponsors, CRO’s, representatives of the IRB/REB, and regulatory agencies). The subject’s name will not be used in any public report of the study.

### Data storage

All data will be stored on REDCap [25] a secure web application for building and managing online databases commonly used in the clinical trials research community. Ongoing auditing will be performed by the LRCP clinical trials unit, independent from the trial investigators and sponsor. All of the biomarker studies described in this section will be performed in [name] laboratory located at the LRCP, in London, Ontario. All specimens will be labeled solely with the patient’s unique study identifier number, stored in a secure facility at LHSC, and will be accessed only by clinical trial staff.

### Adverse events

The severity of adverse events will be evaluated using the Common Terminology Criteria for Adverse Events (CTCAE) version 4.0 grading scale [26]. Any grade 4 or 5 adverse event that is definitely, probably, or possibly the result of protocol treatment must be reported to the Principal Investigator and Central Office within 24 h of discovery. The Serious Adverse Event (SAE) report form is to be completed with all available information and uploaded to the REDCap SAE page. The Central Office must be notified by email or telephone that a new SAE form has been uploaded into REDCap. It is the responsibility of each local Principal Investigator to report all SAEs to their REB as per local REB requirements. The Principal Investigator should also comply with the applicable regulatory requirement(s) related to the reporting of unexpected serious adverse drug reactions to the regulatory authority (ies).

## Data sharing statement

De-identified participant data from this trial will not be shared publicly, however, the full protocol will be published along with the primary analysis of the outcomes.

## Protocol ammendments and trial publication

Trial registration elements are summarized in Additional file 6. Any modifications to the trial protocol must be approved and enacted by the principal investigator (Current version: 1.3 on March 15, 2019). Protocol amendments will communicated to all participating centres, investigators, IRBs, and trial registries by the principal investigator. Any communication or publication of trial results will be led by the principal investigator, and is expected to occur within 1 year of the primary analysis. Trial results will remain embargoed until conference presentation of an abstract or until information release is authorized. Authorship of the trial abstract and ultimately the full manuscript will be decided by the principal investigator at the time of submission. Professional writers will not be used for either abstract or manuscript preparation.

## Discussion

Patients with HPV+ OPC have substantially better treatment response and OS than HPV- disease [3]. This has spurred increasing interest in de-escalation of therapy with the hopes of reducing treatment-related toxicity.

ORATOR2 is a multi-center phase II trial that aims to randomize 140 patients to two de-escalated interventions: de-escalated radiotherapy (± chemotherapy) or TOS (± adjuvant radiotherapy). The primary radiotherapy arm is based on the chemoradiation arm of HN002 [15] and the TOS arm is partially based on the treatment paradigm of ECOG-3311 [16].

This trial will assess the safety of both of these de-escalation approaches, comparing each to historical controls, and will allow for comparisons of OS, PFS and QOL between the two interventions. There is a paucity of data comparing primary RT and primary surgical approaches to oropharyngeal cancers. To date, the only randomized study examining this question is ORATOR, which enrolled patients regardless of HPV status, and included a small number of patients. ORATOR2 will allow for an assessment of both approaches in the early T-stage HPV+ patient population. Furthermore, the ORATOR trial can be used for additional historical controls, with a planned comparison between HPV+ patients in ORATOR (who were treated with more aggressive approaches) and ORATOR2 to assess differences in QOL and time-to-event outcomes.

A recruitment video has been created to help patients and the public understand the rationale and design behind the trial, and to help reach the target accrual (www.orator2.com).

Results of ORATOR2 are expected to provide data that will help guide treatment decisions in the management of HPV-associated OPC, which remains one of the most contentious issues in head and neck oncology.

## Data Availability

Not applicable.

## Abbreviations

AJCC: American Joint Committee on Cancer
CRF: Case report form
CRT: Chemoradiation
CT: Computed Tomography
CTC-AE: Common Toxicity Criteria for Adverse Events
ECOG: Eastern Cooperative Oncology Group
ENE: Extranodal extension
EORTC H&N35: European Organisation for Research and Treatment Quality of Life Questionaire, Head and neck module
EORTC QLQ-C30: European Organization for Research and Treatment of Cancer Quality of Life Questionnaire, Core Module
FDG: Fluorodeoxyglucose
HPV: Human papillomavirus
HPV-: Human papillomavirus negative
HPV+: Human papillomavirus positive
IMRT: Intensity modulated radiotherapy
LHSC: London Health Sciences Centre
LN: Lymph nodes
LRCP: London Regional Cancer Program
LVI: Lymphovascular invasion
MDADI: MD Anderson Dysphagia Inventory
NCI-CTC: National Cancer Institute Common Toxicity Criteria
NDII: Neck Dissection Impairment Index
OAR: Organ at risk
OPC: Oropharyngeal squamous cell carcinoma
OS: Overall survival
PCR: Polymerase Chain Reaction
PET: Positron-Emission Tomography
PFS: Progression-free survival
PNI: Perineural invasion
PNQ: Patient Neurotoxicity Questionnaire
QA: Quality Assurance
QOL: Quality of Life
RP: Retropharyngeal nodes
RT: Radiotherapy
TLM: Transoral laser microsurgery
TORS: Transoral robotic surgery
TOS: Transoral surgery
VHI-10: Voice Handicap Index-10
VMAT: Volumetric Modulated Arc Therapy
